### 2.9. Data Management and Quality Assurance

Data will be recorded on standardised collection forms and then entered into a protected electronic database accessible only to authorised members of the research team. Participant identifiers will be stored separately from outcome data, and each participant will be assigned a study code. Data checks will include verification of missing fields, range plausibility, and consistency across time points. Only de-identified data will be used for analysis and reporting.

Fidelity procedures will include provider training before intervention delivery, use of session templates and attendance logs, and documentation of relevant deviations or unusual events. Written standard operating procedures will be used to support consistency in assessment, intervention progression, and adverse-event recording. Any protocol amendments affecting eligibility, outcomes, or procedures will be documented and communicated to the participating institutions and research personnel before implementation.

### 2.10. Statistical Analysis

Statistical analyses will be performed using IBM SPSS Statistics, version 32.0 (IBM Corp., Armonk, NY, USA). Analyses will follow the intention-to-treat principle, with all randomised participants analysed in their allocated groups regardless of adherence [49]. Baseline characteristics will be summarised using appropriate descriptive statistics. Mixed-effects models will estimate changes over time and group-by-time differences for each outcome distribution [50]. Models will include group, time, group-by-time interaction, baseline outcome value, and facility as a fixed effect or clustering factor, as supported by the number of participating facilities and model stability.

The primary family comprises the combined-intervention versus usual-care contrasts at T1 for the Stroop interference score, TUG time, and EQ-5D-5L index. The family-wise two-sided Type I error rate will be controlled at 0.05 using Holm’s step-down procedure. Secondary between-arm contrasts and secondary outcomes will be treated as exploratory; within prespecified outcome families and time points, false discovery rate will be controlled using the Benjamini–Hochberg procedure, with both unadjusted and adjusted p-values reported. Follow-up models will examine maintenance only for outcomes collected at T2. Supportive analyses may include per-protocol, adherence-informed, dose-response, and co-intervention-adjusted models. Multiple imputation may be used if missingness is non-trivial and the assumptions are defensible [51] (Table 4).

Results will be reported as adjusted mean differences or appropriate model-based contrasts with 95% confidence intervals. The direction of benefit will be stated explicitly. Adherence will be summarised by arm and component using sessions attended, percentage of planned sessions completed, and total minutes delivered. A factorial coding of exercise (present/absent) and cognitive stimulation (present/absent) will be used in an exploratory exercise-by-cognitive-stimulation-by-time model. Because the trial is not powered for interaction testing and the combined arm has greater contact time, these analyses will be described as hypothesis-generating and will not support confirmatory claims of synergy.

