### 2.5. Randomisation, Allocation Concealment, and Blinding

Randomisation will be performed only after eligibility confirmation, written consent, and completion of baseline assessment. Participants will be allocated 1:1:1:1 within each ERPI using computer-generated lists with randomly varying block sizes. An adjunct professor at Escola Superior de Saúde Jean Piaget de Viseu who has no role in recruitment, baseline or outcome assessment, intervention delivery, or data analysis will generate and hold the allocation sequence. The sequence will be stored in a password-protected file on an institutional computer accessible only to this custodian. After baseline data are confirmed as complete, the facility technical director will send the coded participant identifier to the custodian, who will reveal only that participant’s assignment through individual secure communication. Local staff will retain the revealed assignment and intervention schedule but will not have access to future allocations. Outcome assessors will remain blinded. These safeguards distinguish allocation concealment before assignment from assessor blinding after assignment.

Participants and intervention providers cannot be blinded because of the behavioural nature of the programmes. Outcome assessors will be blinded to group allocation and will conduct assessments using participant lists that include identifiers but not treatment assignment. Participants and staff will be reminded not to disclose intervention participation during assessments. Statistical analysis will use coded group labels until the primary analyses are complete.

Contamination is a realistic risk in residential facilities because residents share social spaces and may discuss activities. To mitigate this, interventions will be scheduled separately where feasible, provider teams will follow predefined procedures, and usual-care activities will be documented monthly. Baseline comparability and any material changes in routine activities will be reported transparently, and sensitivity analyses will consider potential clustering or contamination effects.

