### 2.6. Interventions

All active interventions will be group-based, delivered face-to-face on site, and scheduled three times per week for 12 weeks. Attendance, protocol deviations, and relevant occurrences will be recorded. The combined arm will receive both intervention components during the same visit, which reflects a realistic multimodal delivery model but introduces greater contact time than the single-component arms; this issue will be considered when interpreting comparative effects.

Table 1 summarises the main intervention components. More detailed intervention reporting is provided in Supplementary Material S2.

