#### 2.6.2. Cognitive Stimulation Programme

The cognitive stimulation programme will consist of small-group sessions designed to stimulate executive and broader cognitive domains relevant to daily functioning. Activities will include structured games, riddles, puzzles, orientation tasks, reasoning exercises, inhibition tasks, memory activities, and paper-and-pencil exercises targeting attention, working memory, cognitive flexibility, language, and visuospatial skills [14,15,16].

Tasks will be adapted according to participants’ comprehension and performance, progressing from simpler to more complex activities over the intervention period. Group delivery is intended not only to stimulate cognition but also to reinforce social interaction, motivation, and adherence, which are central to sustainable long-term care programming.

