### 2.8. Sample Size

The target sample size is 140 randomised participants (approximately 35 per arm). This is the pragmatic recruitment target rather than a zero-dropout analysable sample; loss of up to 20% by T1 is anticipated, leaving approximately 112 participants (28 per arm). The sample is feasibility-driven, reflecting the recruitment capacity of the participating facilities and intervention workload. The Torga validation study reported a standard deviation of 0.43 for its inhibitory-control index [33]. With 35 participants in the combined and usual-care arms, a two-sided independent comparison at alpha = 0.05 and 80% power has a minimum detectable difference of approximately 0.67 standard deviations, equivalent to 0.29 index points. If 20% are unavailable at T1 (28 per arm), the corresponding value is approximately 0.75 standard deviations or 0.32 index points. Baseline-adjusted mixed models may improve precision, but these conservative values make clear that the trial is designed to detect moderate-to-large rather than small effects.

The primary estimand is the adjusted between-group difference in change from baseline to T1 for the combined intervention versus usual care. This estimand will be evaluated for the Stroop interference score, TUG time, and EQ-5D-5L index. Effect estimates and 95% confidence intervals will be emphasised. Comparisons involving the exercise-only and cognitive-stimulation-only arms, maintenance at T2, and exercise-by-cognitive-stimulation interaction effects are exploratory because the pragmatic sample was not selected to power those tests.

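### The combined arm is delivered in groups, but the primary model has no delivery-group effect, so its standard errors are understated if the delivery-group ICC is above zero

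*Protocol article*

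**What the plan says.** All references are to the protocol article.

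- **Delivery.** Section 2.6: "All active interventions will be group-based, delivered face-to-face on site". Section 2.6.2 describes small-group cognitive sessions and gives the group a purpose of its own: "Group delivery is intended not only to stimulate cognition but also to reinforce social interaction, motivation, and adherence". In Table 1, usual care is routine institutional activity with no programme from the study team.
- **Allocation.** Residents are randomised individually, 1:1:1:1, within each of four ERPIs (Sections 2.1 and 2.5).
- **Primary model.** Section 2.10 lists arm, time, arm-by-time, the baseline value and "facility as a fixed effect or clustering factor, as supported by the number of participating facilities and model stability". Neither this section nor Table 4 names a delivery-group or facility-by-arm term.
- **Clustering elsewhere.** Section 2.5 says only that "sensitivity analyses will consider potential clustering or contamination effects", without naming a model.
- **Sample size.** Section 2.8: "a two-sided independent comparison at alpha = 0.05 and 80% power has a minimum detectable difference of approximately 0.67 standard deviations". After 20% loss (28 per arm) the figure is about 0.75 SD. The section calls these values conservative.

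**The concern.** Residents who share sessions for 12 weeks share peers, providers and session quality, and the protocol expects the group itself to contribute. Their outcomes may therefore be correlated. In the primary contrast this applies to the combined arm and not to usual care, which makes the design partially nested.

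The facility term does not deal with this. It removes differences common to all arms of an ERPI, whereas a delivery-group effect sits in one arm of that ERPI and passes straight into the arm difference. If such an effect exists, the model as listed treats correlated residents as independent, and the p-values that enter Holm's procedure are too small. The detectable differences in Section 2.8 rest on the same independence and so are not conservative in this respect.

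A separate matter is that the form of the facility term is left to depend partly on model stability, which is seen only after fitting, although the number of sites is already known.

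**Working it through.** **Inputs from the protocol.** 35 per arm randomised and 28 per arm at T1; SD 0.43; two-sided alpha 0.05; 80% power (Section 2.8). Four ERPIs (Section 2.1), allocation within ERPI (Section 2.5).

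**Assumptions, since the protocol gives no figure.** One combined-arm group per ERPI, so group size m = 35/4 = 8.75 or 28/4 = 7; delivery-group ICC 0.02, 0.05 or 0.10; equal group sizes; equal total variance in both arms; no baseline adjustment.

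**Step 1: reproduce the stated figures.** MDD = (1.960 + 0.842) × √(2/n).
- n = 35: 2.802 × 0.2390 = 0.670 SD; × 0.43 = 0.288 points.
- n = 28: 2.802 × 0.2673 = 0.749 SD; × 0.43 = 0.322 points.

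Both agree with Section 2.8.

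**Step 2: what the facility term removes.** In ERPI j, the combined mean is (facility effect j) + (treatment effect) + (group effect j) + error. The usual-care mean is (facility effect j) + error. The difference cancels the facility effect and keeps the group effect.

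**Step 3: variance of the contrast.** Var(combined mean) = (σ²/n)[1 + (m − 1)ICC] and Var(usual-care mean) = σ²/n. Relative to the independence value 2σ²/n, the ratio is V = 1 + (m − 1)ICC/2. The true SE is √V times the model SE, the MDD is multiplied by √V, and a nominal 5% test has true size 2[1 − Φ(1.96/√V)]. For example, with m = 7 and ICC 0.05, V = 1 + 6 × 0.05/2 = 1.15, √V = 1.072 and MDD = 0.749 × 1.072 = 0.803 SD.

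| n per arm (m) | ICC | V | SE ratio | Size of 5% test | MDD, SD (points) | Power at the stated MDD |
|---|---|---|---|---|---|---|
| 35 (8.75) | 0.02 | 1.078 | 1.04 | 5.9% | 0.70 (0.30) | 77.0% |
| 35 (8.75) | 0.05 | 1.194 | 1.09 | 7.3% | 0.73 (0.31) | 72.8% |
| 35 (8.75) | 0.10 | 1.387 | 1.18 | 9.6% | 0.79 (0.34) | 66.3% |
| 28 (7) | 0.02 | 1.060 | 1.03 | 5.7% | 0.77 (0.33) | 77.8% |
| 28 (7) | 0.05 | 1.150 | 1.07 | 6.8% | 0.80 (0.35) | 74.4% |
| 28 (7) | 0.10 | 1.300 | 1.14 | 8.6% | 0.85 (0.37) | 69.2% |

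**Step 4: simulation.** Four facilities, one combined group in each, 9 or 7 residents per arm per facility, a fixed facility effect and no group term, 20,000 runs per scenario. Type I error was 5.7–6.0%, 6.6–7.6% and 8.5–10.4% at ICC 0.02, 0.05 and 0.10. A repeat gave about 5.4–6.0%, 6.8–7.5% and 8.6–10.1%. Both agree with the formula and confirm that the facility effect does not remove the problem.

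**Step 5: more, smaller groups.** With eight combined groups (m = 4.38 or 3.5), the SE ratio even at ICC 0.10 is 1.08 (n = 35) or 1.06 (n = 28). At ICC 0, V = 1.

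**Step 6: the facility term on its own.** With no group effect and a facility share of 10% of the variance, leaving facility out gives a mean SE of 0.245 against 0.235 with it (9 per cell), and a type I error of 4.3–4.4%. Under within-ERPI allocation, omission widens the error bars.

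**The case against.** The best defence is that every figure above is conditional. The protocol gives no ICC, number of groups or group size; small groups would lessen the effect, and at ICC 0.05 or below the SE is understated by at most about 9%. Section 2.5 does promise clustering sensitivity analyses, whose model may stand in a SAP that is not shown. The sample is feasibility-driven, so the MDD only describes it. Baseline adjustment could offset the loss of precision: at ICC 0.05 this needs r² = (m − 1)ICC/2, that is 0.15 or 0.194, a baseline–T1 correlation of about 0.39 to 0.44. Session attendance records may also allow group membership to be recovered.

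Much of this stands and sets the size of the point. It does not remove it. Section 2.10 states what the models will include, and Section 2.8 states independence and calls the result conservative. A sensitivity analysis does not protect the p-values that enter Holm. Baseline adjustment helps power, not type I error, because the model SE shrinks with it.

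Four stronger readings are tempting, and the documents do not support them:

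- **That the primary error bars are too narrow as a matter of fact.** This needs a positive ICC, which the protocol neither gives nor rules out.
- **That the open facility term narrows them.** Section 2.10 includes facility in one form or the other, and Step 6 shows that omission would do the opposite. Coded arm labels during analysis (Section 2.5) also limit the scope for a result-driven choice.
- **That the plan uses cluster-robust errors on four sites.** Uncorrected, these would give about 18–19% type I error, but no such variance is named; within mixed models, a clustering factor most naturally means a random intercept.
- **That clustering raises the MDD to about 0.85 SD (35 per arm) or 0.93 SD (28 per arm).** Those values at ICC 0.05 also use Holm's first step. Holm alone gives 3.2356 × √(2/n) = 0.77 or 0.86 SD, more than half of the rise from 0.67 or 0.75.

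**Conclusion.** The point holds in conditional form. Group delivery in the combined arm only, a listed primary model with no delivery-group effect and an independence-based MDD called conservative together mean that the standard errors for combined versus usual care are understated whenever the delivery-group ICC exceeds zero.

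The size is modest at low ICC and material at 0.10. Across ICC 0.02 to 0.10 with one combined group per ERPI, the SE is understated by a factor of 1.03 to 1.14 at 28 per arm (1.04 to 1.18 at 35), and the nominal 5% level becomes roughly 5.4% to 10%. These figures rest on the assumed ICC and group count.

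The undecided form of the facility term is a separate, smaller prespecification matter and not a cause of narrow error bars.

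**What to change.** 1. **Record a delivery-group identifier** for each resident in an active arm. This is one extra field, best added before recruitment starts.
2. **Make the primary model partially nested.** Use a random delivery-group intercept in the active arms, treat each usual-care resident as a singleton, and apply Satterthwaite or Kenward-Roger degrees of freedom. With one group per active arm per ERPI, the variance would be pooled over 3 × 4 = 12 groups.
3. **Prespecify the sensitivity analyses:** the model without the group term, and analyses with the ICC fixed over 0.02 to 0.10, because few groups estimate the variance poorly.
4. **Amend Section 2.8.** Drop the description as conservative or show the MDD over that ICC range, with any Holm adjustment shown separately.
5. **As a separate point, fix ERPI as a fixed effect now** (three indicators), since there are four sites and allocation is made within them.

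The cost is one data field and changes of wording. The downsides are somewhat wider intervals, few degrees of freedom for the group variance, and an assumed common group variance across three different programmes. With one group per arm per ERPI, the group effect also cannot be told apart from a treatment effect that varies between facilities, and the write-up should say so.

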### 2.11. Safety Monitoring and Adverse Events

The interventions are considered low risk, but adverse events may include fatigue, transient pain, dizziness, hypotension, fear of falling, emotional discomfort during cognitive tasks, or exacerbation of pre-existing symptoms. During assessments and intervention sessions, staff will monitor participants for signs of discomfort or instability. If clinically indicated, sessions will be interrupted and institutional or medical follow-up will be initiated according to local procedures.

All adverse events and unusual occurrences will be recorded, together with their timing, severity, management, and whether they appear related to study procedures. Because this is a behavioural intervention protocol conducted in residential care rather than a drug trial, no formal data monitoring committee has been convened. Oversight will be exercised by the principal investigators and collaborating institutions, with transparent reporting of harms in the final trial report.

### 2.12. Trial Status

At the time of manuscript submission, participant recruitment, baseline assessments, intervention delivery, and follow-up had not yet started. Consequently, the flow diagram provided in Figure 1 is presented as a planned CONSORT-style diagram, and all references to screening numbers, allocation totals, retention, and outcome data are intentionally omitted from the present manuscript.

## 3. Discussion

This protocol describes a pragmatic four-arm randomised trial addressing a practical long-term care question: whether a combined physical exercise plus cognitive stimulation programme improves executive function, mobility, and health-related quality of life compared with usual care, and how the estimates from exercise-only and cognitive-stimulation-only programmes compare. The design extends a simple intervention-versus-control trial by placing all four strategies under common eligibility, assessment, and facility conditions. This component-specific information is relevant because the programmes differ in professional requirements, materials, scheduling demands, participant preferences, and implementation costs.

The intervention model is clinically plausible: multicomponent exercise targets capacities required for transfers, walking, and fall prevention, while cognitive stimulation targets attention, inhibition, working memory, and problem-solving relevant to daily function. The combined programme may produce broader effects, but greater weekly contact time prevents a simple causal interpretation as synergy. Dose- and adherence-informed analyses will aid interpretation but cannot remove this structural difference. Formal interaction results will therefore remain exploratory and hypothesis-generating.

Strengths include implementation in real-world long-term care facilities, blinded outcome assessment, multiple active comparison arms, standardised fidelity monitoring, and clinically meaningful outcome domains. The six-month follow-up will provide information on maintenance of the primary outcomes and selected cognitive measures. The TIDieR-based supplementary description supports replication by specifying providers, materials, dose, progression, tailoring, and fidelity procedures.

The trial also has limitations. Participants and providers cannot be blinded, usual care may vary across facilities, and facility culture or staffing may influence adherence. The target sample is pragmatic and may be underpowered for small effects, many secondary outcomes, and formal exercise-by-cognitive-stimulation interactions. Attrition by the six-month follow-up may further reduce precision and introduce bias if loss to follow-up is differential; retention will therefore be reported by arm and addressed through mixed models and sensitivity analyses. Most secondary outcomes are assessed only at T0 and T1, so their long-term maintenance cannot be evaluated. No residents or public contributors were formally involved in designing the original protocol. The cognitive-stimulation component extrapolates evidence derived largely from people with dementia to residents without a major neurocognitive disorder, and its effectiveness in this population remains uncertain. Excluding residents unable to provide consent or follow instructions also limits generalisability to those with more severe cognitive impairment. Finally, the combined arm’s greater contact time precludes confirmatory mechanistic claims of synergy.

If the interventions demonstrate clinically meaningful benefits, the findings will inform scalable strategies to preserve mobility, cognition, and well-being in long-term care settings. Even modest effects may be relevant when programmes are safe, feasible, and integrated into routine care. Conversely, if single-component programmes provide benefits comparable to the combined programme, facilities with limited staffing may prioritise the component most aligned with local needs and resources. The trial will also provide useful information about recruitment, retention, intervention dose, adverse events, and outcome responsiveness for future confirmatory research and may help define realistic implementation pathways in long-term care.

## 4. Conclusions

This protocol presents a pragmatic, randomised trial whose primary objective is to estimate the effect of combined physical exercise plus cognitive stimulation versus usual care on executive function, functional mobility, and health-related quality of life at 12 weeks in older adults residing in long-term care. Secondary and interaction analyses will provide exploratory estimates of the isolated and combined components, while the six-month assessment will examine maintenance of prespecified outcomes. The findings may inform future confirmatory trials and feasible strategies for preserving mobility, cognition, and psychosocial well-being in long-term care.

